## Abstract

**Background:**

Evidence-based medicines, technologies, and protocols exist to prevent many of the annual 300,000 maternal, 2.7 million neonatal, and 9 million child deaths, but they are not being effectively implemented and utilized in rural areas. Nepal, one of South Asia’s poorest countries with over 80% of its population living in rural areas, exemplifies this challenge. Community health workers are an important cadre in low-income countries where human resources for health and health care infrastructure are limited. As local women, they are uniquely positioned to understand and successfully navigate barriers to health care access. Recent case studies of large community health worker programs have highlighted the importance of training, both initial and ongoing, and accountability through structured management, salaries, and ongoing monitoring and evaluation. A gap in the evidence regarding whether such community health worker systems can change health outcomes, as well as be sustainably adopted at scale, remains. In this study, we plan to evaluate a community health worker system delivering an evidence-based integrated reproductive, maternal, newborn, and child health intervention as it is scaled up in rural Nepal.

**Methods:**

We will conduct a type 2 hybrid effectiveness-implementation study to test both the effect of an integrated reproductive, maternal, newborn, and child health intervention and the implementation process via a professional community health worker system. The intervention integrates five evidence-based approaches: (1) home-based antenatal care and post-natal care counseling and care coordination; (2) continuous surveillance of all reproductive age women, pregnancies, and children under age 2 years via a mobile application; (3) Community-Based Integrated Management of Newborn and Childhood Illness; (4) group antenatal and postnatal care; and 5) the Balanced Counseling Strategy to post-partum contraception. We will evaluate effectiveness using a pre-post quasi-experimental design with stepped implementation and implementation using the RE-AIM framework.

**Discussion:**

This is the first hybrid effectiveness-implementation study of an integrated reproductive, maternal, newborn, and child health intervention in rural Nepal that we are aware of. As Nepal takes steps towards achieving the Sustainable Development Goals, the data from this three-year study will be useful in the detailed planning of a professionalized community health worker cadre delivering evidence-based reproductive, maternal, newborn, and child health interventions to the country’s rural population.

**Trial registration:**

ClinicalTrials.gov Identifier: NCT03371186, registered 04 December 2017, retrospectively registered.

**Electronic supplementary material:**

The online version of this article (10.1186/s13012-018-0741-x) contains supplementary material, which is available to authorized users.

## Background

Under-utilization of life saving services during the “Golden Thousand Days,” from conception to age two, continues to be a critical gap in reducing maternal, neonatal, and child morbidity and mortality in low-income countries [1–3]. Evidence-based medicines, technologies, and protocols exist to prevent many of the annual 300,000 maternal, 2.7 million neonatal, and 9 million child deaths, but they are not being effectively implemented and utilized in rural areas [4–6]. Nepal, one of South Asia’s poorest countries and over 80% rural, is a paradigmatic case of these challenges. Mortality rates are high and unequally distributed, with rural impoverished districts bearing much of the burden [7].

Community health care workers (CHWs) are an important cadre of health care workers in low-income countries where human resources for health rural health care infrastructure are limited [8–11]. As local women, they are uniquely positioned to understand and successfully navigate barriers to health care access. Since founding the Female Community Health Volunteer (FCHV) program in 1988, Nepal has relied largely on this network of lay volunteers to act as connecters between the community and the health care system. During the last three decades, the role of the FCHVs has evolved and they have taken on various activities including health promotion, distribution of preventive health commodities, and home-based health care provision, using algorithms to diagnose and treat childhood illnesses and make referrals when needed [12]. Despite the comprehensive range of services provided by FCHVs for reproductive, maternal, newborn, and child health (RMNCH), the evidence shows that under-utilization of evidence-based interventions persists [7, 13].

Policy makers and health care experts in Nepal are considering how to achieve the 2015 Sustainable Development Goals. The Ministry of Health, in addition to other researchers, has identified some major issues with the FCHV program as outlined in their 2014 national FCHV survey and report [14]. The quality of work of FCHVs varies greatly across the country, and services are not tailored to the needs of diverse populations. The various activities conducted by FCHVs are organized by several different and autonomous divisions in the central government. This leads to a lack of coordination, gaps in support and supplies, and often duplication of training and service provision [12]. As these various vertical programs have added activities, FCHVs are not participating successfully in the newer ones [14]. This may be due to the capacity of the current cadre of FCHVs to take on and integrate many new activities. The only requirement for the selection of an FCHV is that she is a married woman who lives in the community she serves. There has been no minimum education requirement, and the national survey of FCHVs in 2014 indicated that 67% of FCHVs attended school, and only 14% graduated from 10th grade (standard high school education in Nepal) [14]. Low participation may also be due to the limited time that FCHVs are spending on their work—only 3 h per day or 2 days per week. Additionally, FCHVs are very loosely integrated into the management system of the public health care system. They thus have little supervision or performance evaluation [14]. The FCHV program from the late 1980s needs to be re-envisioned to meet the Sustainable Development Goals.

Globally, there have been efforts to professionalize CHWs, including minimal education requirements and full-time employment. These efforts have been successful in increasing reproductive and neonatal health care service utilization where CHWs have appropriate training, tools, and supervision, though gaps remain where marginalized and remote populations are not being reached. Additionally, these CHW programs have not been studied at scale to understand effectiveness in larger populations, reach, and cost-effectiveness [15].

Through a public-private partnership in rural Nepal between the Ministry of Health and the healthcare delivery organization *Possible*, we built an integrated CHW intervention that employs full-time, salaried CHWs to deliver evidence-based interventions to improve maternal, newborn, and child health outcomes (see Additional file 1 for a detailed description of the intervention and Additional file 2: Figure S1 for the management structure). *Possible* has found that as rural Nepal has improved education access and retention for girls, there is a sufficient talent pool for hiring local women with a 10th grade education and higher as CHWs. Additionally, rural Nepal has rapidly become technologically connected though mobile phones and cellular data and, like many low- and middle-income countries, can take advantage of mobile applications for health.

*Possible’s* CHWs deliver community-based care facilitated by use of mobile technology [16]. CHWs monitor and promote utilization of services; provide maternal and neonatal health counseling; promote self-efficacy, social support, and emergency planning; and diagnose and refer for major causes of RMNCH morbidity. The evidence-based intervention they deliver is comprised of five integrated components: (1) home-based antenatal care (ANC) and postnatal (PNC) counseling and care coordination; (2) continuous surveillance of all reproductive age women, pregnancies, and children under age two via an integrated electronic health record system; (3) Community-Based Integrated Management of Neonatal and Childhood Illness (CB-IMNCI); (4) group ANC and PNC; and (5) the Balanced Counseling Strategy to post-partum contraception.

We have previously assessed this integrated intervention over an 18-month time-period in a geography covering a population of 33,000. The evaluation demonstrated an increase in key service utilization: institutional birth, ANC visit completion, and use of modern contraceptive methods in the postpartum period. This evaluation was conducted as a pre-post assessment, and several components of the intervention were actively being rolled out during and after the intervention period [17]. The data, however, were encouraging and call for a more rigorous evaluation at scale.

The proposed study will evaluate the efficacy and implementation process of the integrated RMNCH intervention using CHWs as a national pilot. The *Possible* team partnered with Nepal’s Ministry of Health and local health officials to refine and modify the intervention to align with the Nepal Health Sector Strategy 2015–2020 [18]. We chose a type 2 hybrid effectiveness-implementation study to evaluate the effectiveness of the integrated intervention and the implementation process [19]. We utilize the RE-AIM research framework, which has been utilized for other studies of women’s health [20–23] and child health [23, 24], to guide evaluation of the implementation process. The acronym stands for Reach, Efficacy, Adoption, Implementation, Maintenance and is designed to improve the sustainable adoption of effective, generalizable, and evidenced-based interventions that can be scaled and, ideally, shape broader policy environments.

The findings from this study will be used to inform the development of a new system for government CHWs in Nepal.

### Evidence for the integrated intervention

*Possible’s* experience in improving RMNCH in rural Nepal initially centered on facility-based expansion of services and quality improvement. A survey conducted from 2011 to 2013 showed a steep increase in utilization of birth services, with institutional birth rising from 30 to 77% [25, 26]. Logistic regression revealed that the presence of comprehensive obstetric services, belief that the hospital is the safest birth location, safety prioritization in decision-making, and higher average income all significantly contributed to this change [26]. With 23% of women still delivering outside of a facility, and minimal reach into the community, *Possible* embarked on designing a community-based strategy for RMNCH [26].

A cadre of local CHWs were employed and trained. The model was intentionally distinguished from Nepal’s longstanding FCHV program. *Possible’s* CHWs have structured management, standardized initial training, ongoing refresher training, and digitally based monitoring and evaluation which fosters accountability. They all have a minimum high school education requirement and receive a salary for full-time work. CHWs refer to government facilities including village clinics ((sub) health posts) and primary hospitals (primary health centers and district hospitals).

RMNCH priorities were defined by the Nepal government and global targets:

comprehensive antenatal, postnatal and safe delivery care, and CB-IMNCI. These interventions have all shown substantial reductions in maternal, neonatal, and early child mortality [27, 28]. CHWs visit all pregnant and postpartum women to deliver ANC and PNC counseling and prepare birth plans with women and their families. The postpartum visits include counseling for mothers alongside CB-IMNCI for their newborns and children under age two. The CB-IMNCI tool has been validated by a number of studies worldwide [29] and has widespread use globally, including in Nepal [30].

Recognizing that women were being missed and identified late in their pregnancies, *Possible* started pregnancy surveillance for all reproductive age women. Every 3 months, women are asked about their last menstrual period and offered a pregnancy test if pregnancy is suspected. Early pregnancy detection is linked to better birth outcomes, likely due to early initiation of ANC and reduction of high risk behaviors [31]. Additionally, early pregnancy awareness is important to help women with undesired pregnancies access safe and legal abortion care.

In an effort to build social support and women’s empowerment, *Possible* began group care, based upon Centering Pregnancy [32, 33], to complement home visits. This is a model of facilitated groups throughout pregnancy that include health assessments and self-care activities; education, support, and socialization; and ongoing outcome evaluation. By bringing together pregnant women of similar gestational ages, the program makes efficient use of time for antenatal counseling and testing, while allowing facilitators to focus on women’s experiences and concerns. Women also develop a network of peer support during what can be a challenging time. In the rural Nepal context, these groups became an important modality for strengthening care and increasing trust in local village clinics and decentralizing ultrasound and prenatal lab services (Bangura A et al: Measuring fidelity, feasibility, costs: an implementation evaluation of a cluster-controlled trial of group antenatal care in rural Nepal, in preparation; Thapa P et al: Group compared to individual antenatal care: a cluster-controlled trial in rural Nepal, in preparation). These life-saving diagnostic services are not generally available at government clinics and enable CHWs to identify high-risk patients who may require referral to a higher level facility for further care and delivery.

*Possible* then layered postpartum contraception onto the PNC counseling during home visits. Research on interventions to improve postpartum contraception suggests that strategies that bridge the continuum of reproductive health care are more effective than short-term, stand-alone counseling sessions [34]. *Possible* adapted a postpartum contraception counseling strategy for the community setting to bring women’s desires and concerns into a shared decision-making process. The counseling method, called the Balanced Counseling Strategy, is based on a tool developed by the Population Council that has been previously piloted in multiple countries and is in accordance with the World Health Organization’s tiered effectiveness guidelines [35]. Prior studies in clinical settings in Nepal have demonstrated increased uptake of modern contraceptive methods, especially of long-acting reversible contraception, with the use of the Balanced Counseling Strategy [35–38].

There is limited, but growing evidence that mobile technology tools can enhance CHW effectiveness in the realm of reproductive health [39–41]. *Possible’s* CHWs utilize the smartphone application CommCare (Dimagi) for surveillance, care coordination, decision support, and enhanced counseling [42]. The application allows for simultaneous data collection, which is the primary source of information for quantitative evaluation of the entire integrated intervention.

## Methods

### Study aims

We will conduct a type 2 hybrid effectiveness-implementation study of an integrated RMNCH intervention within an approximate population of 300,000 people in rural Nepal. We will study the integrated intervention as it is rolled out in a stepped fashion in two districts in rural Nepal, Achham and Dolakha.

This intervention integrates five evidence-based approaches for reproductive, maternal, newborn, and child health: (1) home-based ANC and PNC counseling and care coordination; (2) continuous surveillance of all reproductive age women, pregnancies, and children via mobile application; (3) CB-IMNCI; (4) group antenatal and postnatal care; and (5) the Balanced Counseling Strategy to post-partum contraception (described in more depth in Additional file 1 and Additional file 2: Figure S1). These integrated programmatic interventions are implemented by the non-profit organization *Possible* in partnership with the Ministry of Nepal.

### Study site

The study will take place in Achham and Dolakha districts of Nepal. The intervention will be implemented in step-wise fashion across the village clusters in coordination with district authorities and study staff.

Achham is located in the hilly far western region of Nepal, home to the highest under-five mortality rates in the country at 82 (one in 12) deaths per 1000 live births [43]. This region has suffered the consequences of war, long-standing poverty, and a concentrated HIV epidemic. *Possible* implements community health care delivery programs and independently manages the government-owned district-level Bayalpata Hospital, a 50-bed facility that serves approximately 80,000 outpatients and 2000 inpatients per year. CHW services in Achham will be expanded to 40 village clusters with approximately 200,000 people.

The second location will be in Dolakha district, one of the hardest hit districts and the epicenter of the second earthquake in 2015 [44]. Upon invitation by the Ministry of Health, *Possible* began managing Charikot Hospital in Dolakha in January 2016. Charikot Hospital is a 35+ bed facility that treats approximately 50,000 outpatients each year. The intervention will be scaled up district-wide during the course of the study. Forty village clusters with approximately 100,000 people will be included.

### Study population

The study population will include women of reproductive age (between ages 15–49) and children from 0 to 24 months of age enrolled in continuous surveillance, home-based care, and/or monthly group ANC led by *Possible’s* team in Achham and Dolakha. Specifically, this will include patients receiving health care services at Bayalpata Hospital in Achham and Charikot Hospital in Dolakha or household-level care through networks of CHWs across both districts.

Staff members involved in the program will be approached for key informant interviews (KIIs) and focus group discussions (FGDs). For all qualitative methods, we will use purposive sampling aiming to maximize heterogeneity across sex, socioeconomic position, health care issues, geographic location, age, caste-class, and other attributes. KIIs will be conducted with participants of the group ANC groups, recently delivered women, women receiving antepartum and postnatal home-based care, and reproductive age women receiving pregnancy screening. KIIs will also be conducted with team members who implemented the interventions, community leaders, and government leaders.

Participants eligible for inclusion in the study include the following: (1) married, reproductive-aged women 15–49; (2) reproductive-aged women 15–49; recently delivered in past 2 years; (3) reproductive-aged women 15–49 with active pregnancy during study period and identified by a CHW serving their village; (4) children aged 0–2 of recently delivered mothers (population 2 or 3 above); and (5) health care staff members including CHWs serving village clusters, research performance site employees involved in study design, program implementation, data collection, or data analysis processes. Study populations 1–4 must reside in either Achham or Dolakha.

Individuals meeting inclusion criteria, as stated above, will be included in the study without exclusion unless (1) individuals migrate from the study before completion of any of the integrated interventions or (2) individuals explicitly request exclusion from the study and decline to consent to the study.

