### Sample size

This implementation research study uses a census methodology rather than a representative sample. The programmatic intervention aims to reach all individuals within the catchment area population given the research performance site’s care mandate to serve this population. All individuals in the catchment area population, as defined under study site above, who meet the inclusion criteria will be approached for inclusion into the programmatic intervention, for which their de-identified clinical data will be analyzed towards the primary aim. The sample size is determined by the overall population covered in the two districts of 300,000, (rather than calculated via a sample size formula) within which we anticipate approximately 8000 deliveries per year or 12,000 during the first 18 months of the study during which enrollment will occur.

To calculate power for the primary outcome of institutional birth rate, we consider a Poisson regression model with 0.05 significance level and two-sided power of 80 or 90%. We further assume a 1-year exposure mean per child over the course of the intervention. We will consider models where the secular trend and other covariates explain 25 or 50% of the total variance in mortality. We assume intra-cluster correlation of outcomes would range from 0.2 to 0.8 for design considerations. Based on these parameters and recent advances in stepped wedge methodology [47], we calculated a design effect ranging from 0.3 to 0.8 to account for the wedge design. To be conservative, we further included a multiplicative design effect of 2.5 to account for cluster randomization, resulting in an overall design effect of 1.8 at a maximum.

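### Excluding people who migrate before completing the intervention is a post-enrolment rule with no counterpart at baseline; it conflicts with the stated census and may bias the before-after contrast

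*Protocol article*

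**What the plan says.** All of the relevant text is in the Methods of the protocol article.

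- **Study population, exclusions.** People who meet the inclusion criteria stay in the study with two exceptions. The first is that "individuals migrate from the study before completion of any of the integrated interventions". The second is a request to be left out together with refusal of consent.
- **Study population, opening.** Women and children are described as those "enrolled in continuous surveillance, home-based care, and/or monthly group ANC led by" the implementing organisation. The next sentence adds "patients receiving health care services at Bayalpata Hospital in Achham and Charikot Hospital in Dolakha or household-level care".
- **Study population, eligibility list.** The four participant groups other than staff are defined by age and by marital, pregnancy, delivery or child status. The pregnancy group reads "reproductive-aged women 15–49 with active pregnancy during study period and identified by a CHW serving their village". A closing sentence states that "Study populations 1–4 must reside in either Achham or Dolakha".
- **Sample size.** "This implementation research study uses a census methodology rather than a representative sample". Everyone eligible in the catchment is to be approached, and the catchment is the one set out under Study site: 40 village clusters in each district.
- **Study design and Data analysis.** Baseline is taken at the beginning of each step. The effect is estimated against the volunteer-based standard of care at that baseline.

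**The concern.** An exclusion that depends on a later event is a problem in any before-after comparison unless it acts equally on both sides. Here the event is migration before some stage of the intervention is complete. Under the baseline standard of care there is no integrated intervention to complete, so the rule has no direct equivalent there. The two periods can then differ in who is counted, quite apart from any effect of the programme.

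The primary outcome is the proportion of women delivering in a facility. If people who leave differ from people who stay in where they deliver or whether they use contraception, removing them moves the rate in the intervention period. For under-two mortality, dropping a child who leaves also drops the time that child was observed alive in the study area.

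The rule also means that the analysed group is not the census the plan claims, and the limitations paragraph in the Discussion does not mention this. The point does not depend on a missing analysis plan: an eligibility exclusion is stated here, and a later analysis plan may be unable to undo it if data on excluded people are not kept.

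**Working it through.** **1. The plan's own figure.** Deliveries expected in the first 18 months: 8000 per year × 1.5 years = 12,000, which matches Sample size. The document gives no migration rate, completion rate or trial baseline for facility birth, so it contains no bias figure to reproduce. The inputs in steps 2, 4 and 5 are assumptions unless a source is named.

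**2. Shift in the institutional birth rate.** Let m be the share excluded, p_s the rate in those who stay and p_m the rate in those excluded.

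- Rate with everyone kept: (1 − m)·p_s + m·p_m
- Rate after exclusion: p_s
- Shift = m × (p_s − p_m)

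| Share excluded | gap 10 points | gap 20 points | gap 30 points |
|---|---|---|---|
| 5% | 0.5 | 1.0 | 1.5 |
| 10% | 1.0 | 2.0 | 3.0 |
| 20% | 2.0 | 4.0 | 6.0 |

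This is the error in the contrast if the baseline is untouched by similar selection. If the baseline is also selected on staying, the net error is m₁ × gap₁ − m₀ × gap₀, which may be smaller. If migrants use facilities more than stayers, the sign reverses.

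**3. Compared with the target.** Data analysis hypothesises a 15% increase without saying whether it is relative or absolute. The only facility-birth rates in the document are 30% and 77%, from a 2011-2013 survey, not from the trial baseline.

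- Relative, from 30%: 0.15 × 30 = 4.5 points
- Relative, from 77%: 0.15 × 77 = 11.6 points
- Absolute: 15 points

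The assumed shift therefore runs from minor to larger than the smallest version of the target.

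**4. Bias, not power.** Assume 6000 deliveries per period, deflated by the stated maximum design effect: 6000/1.8 = 3333. In a simple two-proportion comparison at the 5% level:

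- A 20% loss of deliveries lowers power for a 15% relative rise from 30% only from 97.6% to 94.0%.
- A false shift of 3 points with no true effect would be declared significant with probability 75% at a rate of 30%, 69% at 50% and 85% at 77%.

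**5. Under-two mortality.** A child who has died cannot later migrate, so dropping children who leave alive can remove births while keeping deaths. Take an assumed 40 deaths per 1000 and 5% of births dropped, all of them survivors observed for nearly the full two years: 40/0.95 = 42.1, a shift of 2.1 against a hypothesised reduction of 2 per 1000. This is an upper bound, because children who leave early would have contributed little time in any case.

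**6. The wording of the rule.** Completion of any of the interventions can mean completing even one component, in which case few people are removed, or completing all of them, in which case many are. The 20% row in step 2 needs the second reading.

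**The case against.** The strongest case on the other side has four parts.

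- **The narrow reading.** If the rule removes only people who leave before completing a single component, the number lost may be small. This stands as a limit on size. It does not remove the asymmetry, and the ambiguity is itself a reason to rewrite the clause.
- **The baseline may be selected too.** Baseline is taken at step start and eligible women include those who delivered in the past two years, so women who delivered and then left may already be absent. This stands. One cannot say that the baseline keeps everyone, nor that the bias is upward.
- **The gain is partial.** A woman who leaves before delivery has an unknown place of birth with or without the exclusion. This also stands. For the primary outcome, what is recovered is women who delivered and then left.
- **Analysis sets and censoring usually belong in the analysis plan.** True in general, but this exclusion is stated in the protocol and acts before any analysis set is formed.

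Two stronger readings are tempting and are not supported. A reader might infer that hospital patients from outside the clusters enter with the primary outcome already met. However, the eligibility groups contain no hospital-use criterion, and hospital care is joined to household-level care by an alternative. Sample size ties inclusion to the catchment under Study site, and Data collection takes effectiveness data from the community mobile system with baseline and endline set per cluster. A reader might also infer that only women who complete the programme remain in the intervention period. The rule removes migrants only; residents who stay and complete nothing are kept.

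**Conclusion.** The point holds for the migration exclusion. It removes otherwise eligible people for a post-enrolment event tied to the intervention, cannot operate in the same way at baseline, and conflicts with the catchment census. It may bias the before-after contrast for institutional birth and contraception, and it discards child time at risk.

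Size and direction cannot be fixed from the document. The range of 0.5 to 6 points rests wholly on assumed inputs (5-20% excluded, 10-30 point gap) and on no offsetting selection at baseline. For mortality the error could run in the opposite direction, against the intervention.

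The hospital sentence is an inconsistency of wording to reconcile. It does not show that the sample is selected on the outcome.

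**What to change.** 1. Delete exclusion (1) in Study population.
2. State one denominator for both periods: all deliveries and all children of women enumerated as residents of the study clusters at the relevant date, whatever services they used.
3. Keep the outcomes and person-time of out-migrants up to last contact, and censor child and contraceptive follow-up at the date of migration.
4. Add a missing-outcome sensitivity analysis for deliveries that occur after migration and whose place is unknown.
5. Reconcile the sentence on hospital patients, and the district-level residence wording, with the cluster catchment in Study site and Sample size.

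The cost is a change to the eligibility and analysis-set wording, recording of migration and last-contact dates, and one sensitivity analysis. Some delivery places will remain unknown, but the loss will be visible and can be bounded. The change reduces the risk of bias under either reading of the completion clause.
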